### Sample size

The sample size needed to detect a difference in the primary outcome (IPV reduction) between the intervention group and the control group will be 252 per group, based on sample size calculations using results from previous studies testing a similar intervention in which a difference of 7 % was detected between the intervention and control group on intimate partner violence experience following the intervention [23].^1^ Nurse researchers will be able to screen between one to five women per clinic session. Based on previous studies [4], we estimate that 25 % of women will report experiencing physical or sexual violence from their partner in the last 12 months. Nurse researchers will interview and randomize the eligible participants as well as those who are not eligible for the RCT but who are eligible for the sub-studies based on responses in the baseline questionnaire.

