**Methods:**

Following a formative research phase, a randomized controlled trial will be conducted to test a nurse-led empowerment counselling intervention, originally developed for high-income settings and adapted for urban South Africa. The primary outcome is reduction of partner violence, and secondary outcomes include improvement in women’s mental health, safety and self-efficacy. The study aims to recruit 504 pregnant women from three antenatal clinics in Johannesburg who will be randomized to the nurse-led empowerment arm (two 30-min counselling sessions) or enhanced control condition (a referral list) to determine whether participants in the intervention arm have better outcomes as compared to the those in the control arm.

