Some health care providers understand how women's experiences of violence affect their health and the health of their infants, and many in South Africa and elsewhere have attempted to help their patients who are experiencing violence by a partner [20]. However, the evidence base is still limited for intervention strategies in the health sector and the antenatal care setting in particular. Two studies in high-income settings found significant positive results around a nurse-led antenatal intervention for IPV [21, 22]. Others found promising or insignificant results, although there was great variation in intensity and content of the intervention, and small sample sizes meant insufficient power to detect differences between groups [23].

While little evidence exists on effective interventions to identify and address violence in the health sector in low-resource settings, evidence from higher resource settings has shown some elements of promising interventions that could be adapted and replicated in other settings [24]. Empathetic listening is one of the most important elements of effective interventions to address violence. This, combined with discussions about safety planning and options for ending violence can be a valuable and empowering means of problem-solving and building self-efficacy in this context [21–23, 25, 26]. Some studies have found that having a focal person at the health centre who is specially trained on violence and dedicated to the issue can be an important element in responding to violence [27]; others identified support groups as a potentially positive intervention option [28]. In general, research has confirmed the value of interventions to address partner violence in antenatal care settings and suggests that even a single counselling session can result in improved safety behaviours and reduced levels of intimate partner violence [21, 22].

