### Primary outcome

Intimate partner violence will be measured using a modified version of the WHO instrument from the WHO Multi-Country Study on Women’s Health and Domestic Violence against Women [34]. This instrument assesses women’s experience of physical, sexual, and emotional violence as well as controlling behaviours by a male intimate partner. The effect of the intervention on the primary outcome of physical and/or sexual intimate partner violence will be assessed by comparing the percentage of women in the intervention vs. control groups reporting acts of physical and/or sexual partner violence during the study period and by analysing the patterns of frequency and intensity of the violence between the two study groups based on follow up data.

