### Recruitment and randomization

Pregnant women will be screened for eligibility. Those who are at least 18 years old and less than 33 weeks gestation (to allow enough time for the second intervention session) and who are able to communicate in one of the most common local languages (English, Sotho, or Zulu) will be eligible to participate in the randomized controlled trial. Potential participants will also be asked if they have experienced any of a number of forms of partner violence in the past 12 months. Only those reporting that they have experienced physical or sexual violence by their current or most recent partner in the past 12 months will be eligible. Prior to being enrolled, women will also be screened for immediate safety risk. Reported risk of imminent lethal violence by a partner, fear that a child in the home is at immediate risk of lethal violence by the partner, and being at suicidal risk (as determined by having ideation with a plan to commit suicide) will result in an immediate referral and disqualify women from participating.

Women will be recruited during their routine antenatal appointments at primary healthcare clinics in urban Johannesburg. All clinics are part of the district public health service and generally serve very low income communities. The study will be introduced by a research nurse, who will provide a group introduction to the study without identifying the study as being related to violence but rather framing it as a study on women’s health during pregnancy. A study flier will be distributed with the name of the study and a phone number and first name of the research nurse assigned to that clinic site. Interested women will be offered an opportunity to speak to nurses following their routine clinic care or to schedule an appointment for another time.

Randomization will be conducted through block randomization procedures with study arm assignment revealed upon opening of sequential opaque sealed envelopes prepared in Geneva by the Department of Reproductive Health and Research, World Health Organization. Study nurses will not be blinded to study arm; the same nurse who conducts the baseline interview will also randomize eligible participants.

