### Follow up

Women will be followed up either at their six weeks’ post-partum visit, when they come for their post-natal check-up or immunization for their baby, by phone or at a time arranged with the study nurse. An estimated 15 % of loss to follow up is expected based on other studies in this setting.

All women who experience an adverse event or serious adverse event will be followed up until it is resolved or she is in stable care. For the purposes of this study, an adverse event will be defined as any untoward medical occurrence or harmful event that affects the health or well-being of a study participant or her infant while participating in the study. A serious adverse event is defined as any untoward medical occurrence or harmful event that results in the death of a participant or her infant, is life-threatening, requires inpatient hospitalization (other than for routine delivery) or prolongation of existing hospitalization, or results in persistent or significant disability.

A recruitment period of 18 months with an additional 6 months of follow-up will be needed to recruit a sufficiently large sample size, assuming exclusions for ineligibility, refusal to participate, and loss to follow up.

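### 252 per group gives 80% power for a 7-point difference only if control-arm IPV at follow-up is very low (about 11-12% or less) or almost universal (about 95% or more)

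*Protocol article*

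**What the plan says.** Under Sample size, the protocol article says that the number needed to detect a difference in the primary outcome "will be 252 per group, based on sample size calculations using results from previous studies testing a similar intervention", where "a difference of 7 % was detected between the intervention and control group on intimate partner violence experience following the intervention". The sentence ends with a footnote mark. The visible text gives no control-arm rate, significance level, sidedness or power, and does not say whether 7% is absolute or relative.

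The primary outcome is analysed by "comparing the percentage of women in the intervention vs. control groups reporting acts of physical and/or sexual partner violence during the study period", so it is a comparison of two proportions.

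Three other statements bear on the number:

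- Abstract, Methods: "The study aims to recruit 504 pregnant women from three antenatal clinics in Johannesburg". This is 2 × 252, so 252 is the number enrolled per arm.
- Follow up: 15% "of loss to follow up is expected based on other studies in this setting". The same section mentions loss when it justifies the length of recruitment, but not when it gives 252.
- Recruitment and randomization: entry is open to "Only those reporting that they have experienced physical or sexual violence by their current or most recent partner in the past 12 months".

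The Background puts past-12-month physical or sexual partner violence at 25-35% among pregnant women in South African studies. The 25% under Sample size ("we estimate that 25 % of women will report experiencing physical or sexual violence from their partner in the last 12 months") is the expected yield of screening. It is not an outcome rate for the control arm.

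**The concern.** For a fixed absolute difference, the sample size depends heavily on the control-arm rate: small near 0% or 100%, and more than three times as large in the middle. At conventional error rates, 252 per group and 7 points fit together only near the two ends. Every woman in this trial has been abused in the past year, so a control-arm rate near the lower end needs a justification that the visible text does not give. The expected 15% loss narrows the room further.

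What is at stake is how a null result will be read. The article presents 252 as the number needed, so a non-significant result would be taken as evidence against a 7-point benefit. If recurrence is in the middle range, a true 7-point benefit would be missed half to two-thirds of the time. The Discussion already expects the enhanced control condition and the baseline interview to shrink the contrast.

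**Working it through.** **Inputs from the article:** 252 enrolled per arm, 1:1; a 7% difference, read as 0.07 absolute; binary outcome; 15% loss.

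**Assumed:** two-sided 5% and 80% power, with alternatives below. The control rate p1 is scanned, with p2 = p1 − 0.07.

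**Formula (pooled variance), with p̄ = (p1 + p2)/2:**

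n = [1.960·√(2p̄(1−p̄)) + 0.8416·√(p1(1−p1) + p2(1−p2))]² / (p1 − p2)²

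**Step 1: reproduce 252.** Take p1 = 0.1215, p2 = 0.0515, p̄ = 0.0865. The square roots are 0.3975 and 0.3944, so n = (0.7792 + 0.3320)² / 0.0049 ≈ 252. The stated figure is therefore attainable. The formula is symmetric about 50%, so the same n returns near p1 = 0.948, p2 = 0.878.

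**Step 2: allow for loss.** 252 × 0.85 = 214.2, so about 214 followed per arm (428 in all). Solving for n = 214 gives p1 = 0.107 (against 0.037) or p1 = 0.963. The same pair applies if 252 already includes the loss, because about 214 is then the evaluable target.

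**Step 3: control rates at which 7 points is detectable.**

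| Test and power | 252 per arm | 214 per arm |
|---|---|---|
| Two-sided 5%, 80% | ≤12.2% or ≥94.8% | ≤10.7% or ≥96.3% |
| Two-sided 5%, 90% | ≤9.8% or ≥97.2% | ≤8.8% or ≥98.2% |
| One-sided 5%, 80% | ≤14.8% or ≥92.2% | ≤12.9% or ≥94.1% |

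A continuity correction tightens the limits (11.1% in place of 12.2% in the first cell). Reading 7% as relative makes matters worse: about 7,300 per arm at a 30% control rate and about 3,200 at 50%.

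**Step 4: outside those ranges.** At p1 = 0.30, p2 = 0.23, p̄ = 0.265, n = (1.960 × 0.6241 + 0.8416 × 0.6222)² / 0.0049 ≈ 623 per arm. Power (two-sided 5%) follows from the same formula solved for the power term. The detectable difference is the Δ for which n(p1, p1 − Δ) = 214 at 80% power.

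| Control rate | Power for 7 points, 252 per arm | Power for 7 points, 214 per arm | Detectable difference, 214 per arm |
|---|---|---|---|
| 12% | 81% | 74% | 7.4 points |
| 20% | 56% | 50% | 9.7 |
| 30% | 43% | 37% | 11.6 |
| 40% | 37% | 32% | 12.8 |
| 50% | 35% | 31% | 13.4 |
| 80% | 46% | 40% | 11.8 |
| 90% | 63% | 56% | 9.6 |

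**Step 5: set against the population.** The Background's 25-35% is a 12-month figure for pregnant women generally. The trial takes only women who were positive over such a period, so their later rate should be higher than that of unselected women over the same length of time. At the other end, a rate of 95% or more sits badly with the counselling content in The intervention, which describes abuse as coming in phases with quiet spells.

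**The case against.** The best defence is that no arithmetic error is shown. Step 1 obtains 252 at 12.2% against 5.2%, and other standard settings do so too: 9.8% against 2.8% at 90% power, or 10.7% against 3.7% at 80% with 15% loss built in. The assumed rates may be in the footnote, whose absence from the text at hand is not a fault of the plan. This defence stands against a claim that 252 is wrong. It does not remove the constraint: whatever conventional inputs the footnote holds, 252 and 7 points together force an extreme control rate.

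Four stronger readings are tempting, and the article does not support them.

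- **That 252 cannot detect 7 points because all women are IPV-positive at entry.** Power depends on the control-arm rate during follow-up, and that rate is not given anywhere. Entry status makes a low rate hard to defend but does not exclude it.
- **That prorating the 25-35% proves 12% too low.** At constant hazard, 26 weeks gives 1 − 0.75^0.5 = 13% to 1 − 0.65^0.5 = 19%. But the article fixes no six-month outcome window. A woman enrolled at 32 weeks, delivering at 40 (assumed) and seen six weeks post-partum is exposed for 14 weeks, which gives 1 − 0.75^(14/52) = 7% to 1 − 0.65^(14/52) = 11%. Selection for abuse pushes the rate up by an unknown amount.
- **That loss was left out of 252.** The text is silent. If loss is included, the implied control rate is lower still, so the concern remains either way.
- **That the 7% comes from a study the article itself calls underpowered.** The Background's remark that "small sample sizes meant insufficient power to detect differences between groups [23" concerns a group of other studies, and The intervention cites the same reference among trials supporting the model. Planning on an earlier estimate is a judgement, not an error.

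**Conclusion.** The concern holds in a bounded form. If 7% is absolute and the test is two-sided at 5%, 252 per group gives 80% power only at a control-arm IPV rate of at most about 12% or at least about 95%. With 214 followed per arm, or with the loss already included, the limits are about 11% and 96%. In the 20-50% range, power with 214 per arm is 31-50%, and the difference detectable at 80% power is about 10 to 13 points.

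That the true rate lies between the limits is a reasoned expectation: the sample is selected for past-year physical or sexual IPV, while the article cites 25-35% a year in pregnant women generally. It is not a documented fact, because the control-arm rate is not stated and exposure time varies with gestation at entry. The error rates are also assumed, but a one-sided test moves the lower limit only to 14.8% (12.9% with 214 per arm), and 90% power tightens it.

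**What to change.** Keep 504 and rewrite the Sample size paragraph:

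1. Say whether 252 includes the 15% loss, and that about 214 per arm are expected at follow-up.
2. State that 7% is absolute (or relative), and give the control-arm recurrence rate behind 252 with a justification for a sample in which every woman has past-year IPV and exposure time varies. If the footnote already gives the rate and error levels, only the justification needs adding.
3. Replace the single 7% with the difference detectable at 80% power with about 214 per arm, over a range of control rates labelled as an assumption: about 7.4 points at 12%, 9.7 at 20%, 11.6 at 30%, 12.8 at 40% and 13.4 at 50%. The 7% can stay as the earlier result that motivated the trial.

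The cost is a less favourable stated detectable difference. No extra patients, data or visits are needed.

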### Follow up

Women will be followed up either at their six weeks’ post-partum visit, when they come for their post-natal check-up or immunization for their baby, by phone or at a time arranged with the study nurse. An estimated 15 % of loss to follow up is expected based on other studies in this setting.

All women who experience an adverse event or serious adverse event will be followed up until it is resolved or she is in stable care. For the purposes of this study, an adverse event will be defined as any untoward medical occurrence or harmful event that affects the health or well-being of a study participant or her infant while participating in the study. A serious adverse event is defined as any untoward medical occurrence or harmful event that results in the death of a participant or her infant, is life-threatening, requires inpatient hospitalization (other than for routine delivery) or prolongation of existing hospitalization, or results in persistent or significant disability.

A recruitment period of 18 months with an additional 6 months of follow-up will be needed to recruit a sufficiently large sample size, assuming exclusions for ineligibility, refusal to participate, and loss to follow up.

### The intervention

The Safe & Sound intervention is based on a nurse-led "empowerment counselling model". This model has been tested through randomized controlled studies in antenatal care and shown to be effective in improving women's safety, coping, and potentially in reducing violence in the United States [21, 23] and Hong Kong [22]. The empowerment model assumes that the perpetration of intimate partner violence aims to control the behaviour of female partners and that by increasing a woman's sense of control over her life, she can better develop strategies to reduce violence in her relationship [41]. This model promoted by Dutton [26] includes two complementary components-- (a) improving women's safety and protection, including negotiating safer sex with a partner, while (b) enhancing her decision-making and problem solving ability in her relationship.

Safe & Sound is provided by a nurse researcher trained in counselling and covers a combination of the following elements that will be individually tailored depending on women’s experience and her readiness to change:
**Empathetic listening;** also called active listening or reflective listening is a way of listening and responding to another person that improves mutual understanding and trust, including emotional identification, compassion, feeling, and insight.
**Cyclical nature of partner violence:** the nurse researcher will discuss how abusive relationships often follow predictable patterns in which abuse might subside for a period of time, only to resume again later. She will also discuss possible warning signs that could indicate that a renewed phase of violence might be imminent. By better understanding these patterns, the woman should be better prepared to prevent or reduce subsequent violence and to predict signs of increased dang**e**r.
**Evaluating danger and discussing options:** the nurse will help the woman assess her level of risk in her relationship with the violent partner and whether there are signs that the violence will escalate with potential health consequences for her and her pregnancy. If the woman or her children are in immediate danger for their life or if the woman discloses suicidal ideation, she will not be part of the study and will be referred appropriately, as discussed previously. Based on the woman's current risk and the support available to her, the nurse will discuss options for reducing abuse, without providing directives or value judgements. The nurse will recognize that women cannot always safely leave their abusive partners, but that they have options for reducing abuse in their relationship. These options include protecting children from violence, developing safety strategies, accessing community resources for social support, and addressing relationship dynamics with partners.
**Developing safety strategies:** the nurse will help the woman to develop a safety strategy tailored to her situation and based on culturally appropriate actions for increasing personal safety of herself and her children. These strategies include developing a code with family and friends to indicate increased risk, alerting neighbours to the situation and seeking support from them in the case of an abusive incident, having a bag and documents ready in case of the need to flee with children in the event of imminent danger. Safety will also be discussed in relation to abused women’s increased vulnerability to HIV or inability to seek appropriate treatment among HIV positive women, especially PMTCT. The nurse researcher will help the woman identify those behaviours and strategies that she can best implement.
**Pregnancy changes:** based on early piloting of the intervention which suggested women have concerns around relationship and sexuality changes in pregnancy, nurses can begin an open ended discussion around participants’ pregnancy-related concerns, including changes in relationship dynamics, financial needs, or sexual desires that couples might experience during the pregnancy and post-partum period. The approach is to listen empathetically and provide accurate health-related information to a number of concerns (such as perceived danger of sexual intercourse during pregnancy).
**Legal steps:** women who are prepared to take legal steps to protect themselves or their children from a violent partner are given step-by-step instructions for obtaining a protection order. In practice, this process is complex and requires many visits to the magistrate court and police. A ‘job aid’ developed with input from a local legal organization specializing in IPV will be employed. If needed, nurses can refer women to legal aid for support in completing the protection order.
**Available resources:** based on the findings of the formative research, participants will be given a list of organizations or social services available locally that can provide help with the psychological, legal, social, shelter, or health-related needs resulting from violence. All agencies will have been sensitized to the study and have demonstrated capacity to serve as referrals. The nurses will have a choice of giving women a written, verbal, or telephone referral to the external organizations, depending on the preferences of the woman.

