## Methods/Design

A randomized controlled trial (RCT) of a two-session empowerment counselling intervention among pregnant women (*n* = 504) experiencing past-year physical and/or sexual IPV will be carried out at three antenatal clinics in Johannesburg, South Africa. Individual women will be randomized to the intervention or control group, with women in the intervention group receiving the empowerment counselling intervention and women in the control group receiving enhanced standard of care in the form of a list of referrals to local resources.

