The randomized controlled trial (RCT) will test the efficacy of an intervention to address partner violence during pregnancy. Women screening positive for violence and who satisfy the eligibility criteria will be randomized to the intervention or control group (Fig. 1). The intervention group will receive up to two sessions of a counselling intervention and both groups will receive a brief information sheet with local referrals, including for counselling, shelters, legal resources, child protection services, police, and other relevant NGOs. Each of the listed referrals was contacted and its willingness and capacity to respond to referrals during the course of this study was assessed. Selected agencies will be included as active referral options. The protocol complies with the guidelines of the Standard Protocol Items: Recommendations for Interventional Trials (SPIRIT), and all data collection is in compliance with Consolidated Standards of Reporting Trials (CONSORT) guidelines.

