### Data management

Data collection will be done on paper case report forms (CRFs) and data kept in locked cabinets until they are transferred to the central office and reviewed in a data quality check by the data manager. The data manager will also compare responses in the screening logs with responses in the CRFs to confirm the accuracy of the screening logs. Since patient records are not kept at clinics but rather are carried with them from appointment to appointment, the screening logs and some components of the CRFs will be considered source documents for the trial. Screening logs and CRFs will be scanned and uploaded to a secure location accessible by the Geneva data management team. Data entry will occur at WHO in Geneva. Open Clinica software [44] will be used for data management.

The UNDP-UNFPA-UNICEF-WHO-World Bank Special Programme of Research, Development and Research Training in Human Reproduction (HRP) serves as sponsor for the study. Clinical studies supported by WHO are carried out according to the International Conference on Harmonization (ICH) Good Clinical Practice (GCP) standards, and WHO/HRP standard operating procedures (WHO/HRP SOPs) in the design of the study, data collection, management, analysis, and interpretation of data. HRP standard operating procedures (SOPs) for managing clinical trials will be adhered to throughout the trial. These procedures have been used in previous trials sponsored or coordinated by WHO. The roles and responsibilities of all individuals and institutions involved in the design and conduct of the study, including the study sponsor, study staff, study investigators, steering committee, and the Data Safety and Monitoring Board (DSMB) are clearly described in the SOPs. Data quality will be monitored through 100 % visual checking of CRFs and screening logs at site by data manager and through additional visual checks by the data analyst in Geneva. There will also be query reporting once data are entered into the data management system and through file reviews during regular monitoring visits.

Data will be analysed by study arm using an intention to treat analysis and as detailed in a data analysis plan developed for the study. Statistical data will be analysed using Stata [45] and qualitative data from the process evaluation will be analysed using NVivo [46].

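### The counselling text, used only in the intervention arm, repeats a safety exclusion in wording broad enough to permit removal of women already randomised; it must be reconciled with the pre-enrolment screen and the intention-to-treat statement

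*Protocol article*

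**What the plan says.** Four statements in the protocol article bear on this.

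- **Recruitment and randomization** puts the safety check before entry: "Prior to being enrolled, women will also be screened for immediate safety risk". Three findings count: a threat of imminent lethal violence, lethal danger to a child at home, and "being at suicidal risk (as determined by having ideation with a plan to commit suicide". The stated consequence is that any one of them "will result in an immediate referral and disqualify women from participating". This happens before the envelope is opened, so it is neutral between arms.
- **The intervention**, under the element on evaluating danger and discussing options, describes the nurse helping the woman judge her level of risk. It then turns to two situations, a threat to the life of the woman or her children and disclosure of suicidal ideation, and says that in either case "she will not be part of the study and will be referred appropriately, as discussed previously".
- **Methods/Design** has "women in the intervention group receiving the empowerment counselling intervention and women in the control group receiving enhanced standard of care", and the text under **Objectives** adds: "The intervention group will receive up to two sessions of a counselling intervention". The element on evaluating danger therefore belongs to one arm, after allocation.
- **Data management** states: "Data will be analysed by study arm using an intention to treat analysis", with details left to a data analysis plan that is not shown.

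**The concern.** An exclusion applied before randomisation costs eligibility but not comparability. The same exclusion applied during counselling would act on one arm only. Women who disclose acute danger are plausibly more likely than average to report violence at follow-up, and women who disclose suicidal ideation are plausibly more likely to score high on the anxiety and depression scale. If either group left the intervention arm without outcome data while their counterparts stayed in the control arm, the primary comparison and the mental health comparison would both tilt towards the intervention with no effect of counselling.

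The intention-to-treat label does not by itself prevent this. The primary outcome is the woman's own report at follow-up, and an analysis by arm cannot use an answer that was never sought. The same unblinded nurses screen, randomise, counsel and collect data, so a nurse who takes the counselling sentence at its word could reasonably stop pursuing a follow-up interview.

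**Working it through.** **Step 1. The two exclusion statements side by side.**

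| | Recruitment and randomization | The intervention |
|---|---|---|
| Timing | Before enrolment | Within a counselling element; up to two sessions |
| Who reaches it | All women screened | Intervention arm only |
| Danger | Imminent lethal violence to the woman; immediate lethal risk to a child | Immediate danger for the life of the woman or her children |
| Suicidality | Ideation with a plan | Any disclosed ideation |
| Consequence | Referred and disqualified | Referred and not part of the study |

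The consequences match and the second statement refers back to the first. The suicidality wording does not match. A woman with ideation but no plan passes the screen, is randomised, and meets the counselling wording if she mentions the ideation in a session. Separately, danger or suicidality may arise between the screen and a second session. So the counselling sentence can apply to women who were correctly enrolled.

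**Step 2. What one-sided removal would do.** The point disputes no stated figure. The 252 per group and the 7-point difference (Sample size) serve only as a scale. The 252 cannot be reproduced here, because the text shown gives no control rate, significance level or power.

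Inputs:
- n = 252 per arm (Sample size), or 252 × 0.85 ≈ 214 after the expected 15% loss (Follow up).
- p, the true proportion reporting violence in both arms: assumed 25%, 35% or 50%.
- f, the fraction of the intervention arm removed without outcome data: assumed 1%, 2%, 5% or 10%.
- h, the proportion of removed women who would have reported violence: assumed 80% or 100%.

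With no true effect, the observed intervention proportion is (p − f·h)/(1 − f). The spurious difference is p minus that, which simplifies to

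d = f·(h − p)/(1 − f).

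The ends of each range come from p = 50%, h = 80% (low) and p = 25%, h = 100% (high):

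| f | Women of 252 | Low d | High d |
|---|---|---|---|
| 1% | 2.5 | 0.01 × 0.30/0.99 = 0.3 points | 0.01 × 0.75/0.99 = 0.8 points |
| 2% | 5.0 | 0.02 × 0.30/0.98 = 0.6 | 0.02 × 0.75/0.98 = 1.5 |
| 5% | 12.6 | 0.05 × 0.30/0.95 = 1.6 | 0.05 × 0.75/0.95 = 3.9 |
| 10% | 25.2 | 0.10 × 0.30/0.90 = 3.3 | 0.10 × 0.75/0.90 = 8.3 |

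The probability of a false two-sided 5% rejection uses a normal approximation with pooled variance, and n and n(1 − f) women in the two arms. With n = 252 it is about 5% at 1% removed, 5–7% at 2%, 6–18% at 5% and 11–61% at 10%. With n = 214 the last two become 6–16% and 10–54%.

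**Step 3. When the bias vanishes.** d is zero if f = 0, that is, if no randomised woman is removed or if those referred are still followed and analysed. It is also zero if h = p. The direction towards the intervention therefore depends on removed women being at higher risk than average (h > p). That is more secure for women removed because of danger than for those removed because of ideation alone.

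**The case against.** The strongest reply is that the sentence is only a reminder. It says it is repeating something, and the only earlier text on danger or suicidality leading to referral and non-participation is the pre-enrolment screen. Its language is that of not entering a study; it does not speak of withdrawal or discontinuation. Nowhere does the article say that a randomised woman is withdrawn, not followed up or left out of analysis, and it states intention to treat. On that reading the sections agree about who is analysed.

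Most of this stands as an account of the likely intent. A reader might infer from the counselling section that the design does remove the highest-risk women from one arm, and that it flatly contradicts intention to treat. The documents do not support that: both conclusions need the literal reading to be adopted first. Nor do they support saying that control women are never re-assessed. No danger assessment is described for them before follow-up, but adverse events are recorded and followed for all women, and the article does not rule such an assessment out.

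The reminder reading does not explain the wider suicidality wording. A pure restatement would carry the same criterion. Because it does not, the cross-reference fails to settle what happens to a randomised woman who discloses ideation without a plan.

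The objection to the size is also fair. The screen has already taken out the most acute cases, so 5–10% removal is not to be expected without evidence. At the extreme corner (10% removed, all recurring, 25% outcome rate), 10/25 = 40% of the arm's recurrences would leave by this route. Removal of 1–2% costs at most about 1.5 points.

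**Conclusion.** The concern holds as an internal inconsistency that leaves open a route to bias; it is not established that removal will occur. The two sections differ on timing and on the suicidality criterion, and the counselling wording, taken literally where it stands, permits one-sided loss of women already randomised, in tension with the intention-to-treat statement.

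If that happened and outcomes were not collected, the spurious benefit could range from negligible (0.3–1.5 points at 1–2% removed) to more than the whole planning difference of 7 points (up to 8.3 at 10% removed). The removal fraction, the outcome rate and the recurrence among removed women are all assumptions; the documents supply none of them. It deserves correction because uncollected self-reports cannot be recovered at analysis and the remedy is cheap.

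**What to change.** Reconcile the Recruitment and randomization text with the counselling text on two matters: when the exclusion applies, and which suicidality wording is meant. No view is taken here on the clinical criterion; that is for the investigators.

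Then state, in the counselling element and beside the intention-to-treat sentence in Data management, that:

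- exclusion from the study applies only before randomisation;
- a woman referred for danger or suicidality after randomisation, in either arm, stays in follow-up unless she withdraws consent, and stays in her arm for the intention-to-treat analysis;
- post-randomisation referrals of this kind are recorded and reported by arm.

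The referral itself is unchanged. The cost is about two sentences of text, matching instructions to the nurses, and follow-up attempts for what should be a small number of referred women.
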